### Demographics

Upon the patient's entry (T0) into the study the full neurological status and following patient characteristics will be recorded: age, gender, brain lesion site (from status), extent of hemiplegia (the perceived disability as categorised by the patient: no, mild, average and severe disability), time post stroke, ability to imagine motor acts (as perceived by the patient in four categories: no ability, blurry/unfocussed, some/parts, vivid imagery), cognitive level (MMSE), hand dominance prior to stroke. Additional information about highest educational level and sports history (no history, leisure, competition, profession) by asking the patient is recorded as well. Treating therapists are asked to predict, based on their experience, whether patients in the experimental group will benefit from a mental practice based therapy.

We will then investigate whether the two groups are comparable and whether any of these data have prognostic value.

### Main study parameter/endpoint

It is hypothesised that mental practice has the most effects on the movement that is actually mentally rehearsed [9,18,25,26]. Improvement of these activities should therefore be assessed. To measure if mental practice improves the performance of activities in the experimental group more than in the control group, an 11-point Likert scale will be used:

▪11 point Likert scale assesses the performance of the activities 'drinking' and 'walking' ranging from 10 ('excellent') to 0 ('poor') as perceived by the patient and the therapist. The physiotherapist and the occupational therapist will each score another task, which may be individually chosen and scored on the 11 point Likert scale. If the participant is treated for swallowing problems and/or motor problems due to a facial paresis by a speech therapist, he himself and the speech therapist will score motor actions within these two domains on perceived performance.

### Secondary study parameters/endpoints

• Motricity Index (MI – function (impairment) level)

The Motricity Index evaluates voluntary movement activity and the maximum muscle strength with a six point Scale in six limb movements. Reliability and Validity are sufficient in stroke populations [27].

• Barthel Index (BI – activity level)

With the Barthel Index the degree of independent performance of daily activities is measured [28]. Several versions exist. In this study an assessment form with a 20 points scale will be used [28].

• Nine Hole Peg Test (NHPT – function (activity) level)

The NHPT is a measuring instrument in which the speed of the fine hand coordination is assessed. The patient has to take nine dowels from a tray, one at a time, as fast as possible and place them in a pegboard. The time needed to complete the attempt is recorded. Only the hand that is being assessed (i.e. the affected hand) may be used. The reliability and validity are sufficient [29-31].

• Rivermead Mobility Index (RMI – activity level)

This is a staff-completed questionnaire to measure mobility disability after head injury, MS, stroke and other conditions. It comprises of 14 questions (activities scored range from turning over in bed to running) and 1 direct observation of standing for 10 seconds. Each answer is scored 'Yes' (1) or 'No' (0). The minimum score is 0 and the maximum score is 15. The higher the score is, the better the mobility.

• 10 meter walking test (TMW – activity level)

The 10-meter walking test can be used in patients able to walk independently with or without walking aids and/or orthoses. Patients should walk at a comfortable speed. The test is reliable, valid and responsive [27]. Furthermore, a significant relation between the comfortable walking speed during the TMW and the quality with which patients walk has been established [32]. Codes for not able (yet) and independent in wheelchair are 0 resp. 1.

• Timed up and go (TUG – activity level)

The TUG measures the time a patient needs to stand up from a chair, walk 3 meters at a comfortable speed, turn around, walk back and sit down. The patient is allowed to use his/her own walking aids, but no physical assistance may be given by the researcher or therapist. The test is practical and simple. The internal consistency, reliability, validity and responsiveness are sufficient [33-37].

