### Compliance, integrity check and feasibility of mental practice

During the mental practice intervention period, therapy compliance of the patient is monitored by using a log in which the time spent on practice is recorded on a daily basis. The diary entries will be checked by either the therapist or a member of the nursing staff. In the Dutch guidelines the amount of therapy is considered of importance with regard to effectiveness of any intervention to improve functions [2,3,21].

Furthermore, a small sample of the participants will be interviewed by the researcher on experiences and beliefs during mental practice in the experimental group and on content of therapy as usual in the control group (n = 10 in each group for both sites). These will be selected arbitrarily, and limited to those agreeing.

The therapist will be monitored as well. They will be asked to what extent they followed the given instructions from the mental practice protocol. All therapists will be interviewed on their opinion of the feasibility of the experimental intervention in every day practice. To monitor the intervention content an external expert will attend therapy sessions of participants in the experimental group unannounced. Table 1 summarises the data collection.

**Table 1 T1:** Overview of used measures in this study

**Data**	**Time**	**Subject of assessment**
*Demographics*		
Age, gender, time post-stroke; weak side...	T0	Comparison at baseline
MMSE	T0	Comparison at baseline
Psychological assessment	T0	Comparison at baseline
Therapist' prediction on mental practice performance	T0	Comparison at baseline
*Prognostic variables*		
Amount of therapy/training	T0	Prediction on outcome
QEEG	T0	Prediction on outcome

*Primary outcome*		
11 point Likert scale: drinking and walking	T0, T1, T2	Performance on physical level 'activity'
11 point Likert scale: Patient specific tasks	T0, T1, T2	Performance on physical level 'activity'
*Secondary outcome*		
Motricity Index	T0, T1, T2	Performance on physical level 'function'
Barthel ADL scale	T0, T1, T2	Performance on physical level 'function'
Nine Hole Peg Test	T0, T1, T2	Performance on physical level 'function'
Berg Balance Scale	T0, T1, T2	Performance on physical level 'function'
Rivermead Mobility Index	T0, T1, T2	Performance on physical level 'activity'
Ten metres walk time	T0, T1, T2	Performance on physical level 'activity'
Timed up and go	T0, T1, T2	Performance on physical level 'activity'

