### Multivariate analysis

The baseline scores of the patient's demographic, primary and secondary outcomes will be used to compare the two groups. If necessary, adjustments for baseline variables will be made, using analysis of covariance. Differences at baseline and differences between the two groups on the various assessment times will be calculated. Data will be analysed using MAN(C)OVA and Generalized Estimating Equations (GEE) analyses to ascertain the effects of mental practice based therapy on different levels of outcome and to follow improvements individually in time. Regression analyses will be used to identify prognostic variables. The statistical analysis concerned with comparing the two groups will be performed according to the 'intention-to-treat' principle (patients will be analysed in the treatment group to which they were randomly assigned). Missing data will be replaced by a linear interpolation method for missing measurements. A 'last measurement carried forward' method is used to predict outcome in dropouts [44].

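### The 10-metre walk codes non-walkers 0 or 1 and nothing keeps these codes apart from the walk times; analysed as recorded, they would reverse the direction of this secondary outcome

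*Protocol article*

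**What the plan says.** The protocol article, under Secondary study parameters/endpoints, describes who can take the test: "The 10-meter walking test can be used in patients able to walk independently with or without walking aids and/or orthoses". It then gives the rule for the others: "Codes for not able (yet) and independent in wheelchair are 0 resp. 1". The same paragraph mentions speed, but only in support of validity: "a significant relation between the comfortable walking speed during the TMW and the quality with which patients walk has been established".

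Table 1 (under Compliance, integrity check and feasibility of mental practice) lists the outcome as "Ten metres walk time", measured at T0, T1 and T2.

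The section Multivariate analysis says "Data will be analysed using MAN(C)OVA and Generalized Estimating Equations (GEE) analyses". It adds "Missing data will be replaced by a linear interpolation method for missing measurements", carries the last measurement forward for dropouts, and commits the group comparison to intention to treat. It gives no separate treatment for coded values.

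The Study population section sets no walking criterion and admits patients two to ten weeks after stroke. Walking is one of the two tasks that the intervention trains (Experimental intervention).

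**The concern.** On a time scale lower is better, and 0 or 1 second over 10 m is faster than any real walk. The article therefore gives patients who cannot do the test numbers that, in the variable named in Table 1, would be its best values. The code for those not able (yet) shows that the authors expect non-walkers and expect some of them to walk later. If the codes enter the model, the gain of exactly these patients is scored backwards. At stake is the direction of the treatment effect on a listed secondary outcome for a task that the intervention trains.

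**Working it through.** The document gives no figure that depends on the coding, so there is none to reproduce. The check takes the three ways in which the codes could be used.

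**Inputs from the document:** codes 0 and 1; distance 10 m; visits at six weeks and six months.

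**Assumed inputs (not in the document):** non-walkers 30% or 40% in the control arm and 20% in the experimental arm; every walker takes m = 15, 20 or 30 s, the same in both arms.

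**1. Codes analysed as seconds.** Mean time = p × code + (1 − p) × m, where p is the share of non-walkers.

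- Code 0, m = 20: control 0.4 × 0 + 0.6 × 20 = 12.0 s; experimental 0.2 × 0 + 0.8 × 20 = 16.0 s.
- Code 1, m = 20: control 0.4 × 1 + 0.6 × 20 = 12.4 s; experimental 0.2 × 1 + 0.8 × 20 = 16.2 s.
- In general, experimental minus control = (p_C − p_E) × (m − code). This is positive, that is, the wrong way, whenever the experimental arm has fewer non-walkers and the walkers' mean time exceeds the code.
- For a single patient, going from code 0 to a 20 s walk is a change of +20 s, a worsening.

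**2. Codes analysed as speed in m/s.** The walkers' speed is 10/m, and the difference is (p_C − p_E) × (10/m − code).

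- Code 0, m = 20: 0.6 × 0.5 = 0.30 against 0.8 × 0.5 = 0.40 m/s, the right direction.
- Code 1, m = 20: 0.4 × 1 + 0.6 × 0.5 = 0.70 against 0.2 × 1 + 0.8 × 0.5 = 0.60 m/s, the wrong direction. Code 1 equals a walk of 10 m / 1 m/s = 10 s.

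Differences, experimental minus control, over the assumed range. On time a positive value is the wrong way; on speed a negative value is.

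| m (s) | Non-walkers C / E | Time, code 0 (s) | Time, code 1 (s) | Speed, code 0 (m/s) | Speed, code 1 (m/s) |
|---|---|---|---|---|---|
| 15 | 40% / 20% | +3.0 | +2.8 | +0.133 | −0.067 |
| 15 | 30% / 20% | +1.5 | +1.4 | +0.067 | −0.033 |
| 20 | 40% / 20% | +4.0 | +3.8 | +0.100 | −0.100 |
| 20 | 30% / 20% | +2.0 | +1.9 | +0.050 | −0.050 |
| 30 | 40% / 20% | +6.0 | +5.8 | +0.067 | −0.133 |
| 30 | 30% / 20% | +3.0 | +2.9 | +0.033 | −0.067 |

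**3. Codes used only as labels.** Non-walkers then have no score, and the arms are compared among patients who can walk at T1 or T2. That group is formed after randomisation by an ability that the intervention targets.

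**Missing-data rule.** If the codes share the variable with the times, a patient with code 0 at T0, a missing T1 and 20 s at T2 gets an interpolated T1 of 20 × 6/26 = 4.6 s (six months taken as 26 weeks). A non-walker who drops out carries forward 0 s.

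**The case against.** The article calls 0 and 1 codes, not times, and limits the test to independent walkers. A natural reading is that they are data-entry labels recording why no time exists. The document nowhere says that they are analysed as seconds, and an analysis plan that is not shown may settle it. This stands: the reversal is conditional and cannot be stated as what the trial will do. It does not remove the point, because the article itself fixes the numbers beside an outcome named as a time. The label reading also leaves a comparison restricted by walking ability, which sits badly with the intention-to-treat commitment.

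The shares and times above are assumptions, and the document does not say how many patients cannot walk. This also stands, so only the direction is firm, not the size.

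A footnote to Table 1 says that marked measures are used only at the treating therapist's judgement, and the marks are not visible in the text at hand. It is therefore unclear whether every patient is meant to have this test.

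Walking is also covered by measures on which a non-walker can be scored: the 0 to 10 walking rating in the primary outcome, the Rivermead Mobility Index and the Functional Ambulation Categories. That limits the consequence.

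A reader might extend the point to the Nine Hole Peg Test ("The time needed to complete the attempt is recorded") and the Timed up and go ("The TUG measures the time a patient needs to stand up from a chair"), since no value is given there for patients unable to do the task. The document does not support this. It states no code and no wrong rule for either test, and a condensed article may leave such detail to the full protocol or analysis plan.

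**Conclusion.** The point holds for the 10-metre walk, in conditional form. The stated codes do not give a sound outcome on any of the three readings: as seconds both rank best, as speed code 1 ranks as a 10 s walk, and as labels the comparison is limited to walkers selected after randomisation. If the codes are analysed as recorded, the wrong-way difference is 1.4 to 6.0 s on the time scale. If code 1 is analysed as speed, it is 0.03 to 0.13 m/s. Both ranges rest on the assumed shares of non-walkers and walk times.

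A reader might infer that the trial will certainly report recovery of walking as deterioration. The document does not say so. The primary outcome and the sample size are not affected. The coding should be fixed before analysis, but it does not threaten the trial's main conclusion.

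**What to change.** For the 10-metre walk only:

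- Hold ability (not able, wheelchair, walks) in its own variable, so that 0 and 1 never stand in the column of measurements.
- State the metric. Analyse walking as speed in m/s, with 0 m/s for every patient who cannot walk, wheelchair users included. Alternatively, use a rank analysis with all non-walkers worst.
- State that the codes are not interpolated or carried forward as measurements.
- Report the proportion able to walk by arm at each visit beside the speed result.

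The cost is a coding rule and a few lines of analysis text. No new data are needed, because time and ability are already recorded. The downside is that results appear in m/s or ranks instead of seconds.

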### Optional study parameters

• QEEG (Brain-activity – neurophysiological level)

EEG activity in stroke is primarily assessed in the acute phase of stroke recovery to reveal possible epileptic activity [38]. QEEG assessment in the acute and chronic phase of recovery is not a generally performed procedure, although it might function as a reliable marker for monitoring the recovery and predicting the clinical outcomes after stroke [39,40]. In numerous studies, brain electrical activity across the sensorimotor cortex has been related to both execution and imagination of movements. The mu rhythm (8–15 Hz) seems to be connected to movement in general and is only to be found above the sensorimotor cortex [41]. In general, body movements block or suppress mu activity up to 60%, and imagination of movements generates similar suppression. It is hypothesised, that alterations in mu rhythm suppression during motor imagery in stroke would reflect distorted information processing of the sensorimotor cortex, thereby functioning as a possible marker for decreased ability of imagination of movements [42]. In the RCT, we want to investigate if the QEEG can be used as a biomarker to predict if patients are able to perform imagery and are likely to benefit from a mental practice based intervention.

In addition to the QEEG as a prognostic value, the mu suppression is used as an evaluative measure to assess progress in imagery techniques during the six weeks intervention period.

Suppression of the mu waves can be interpreted as movement related information processing. Measures of brain activity will be performed with a universal amplifier (MPAQ, Maastricht Instruments, The Netherlands) and data acquisition software (IDEEQ, Maastricht Instruments, The Netherlands). Eight sensors will be placed above the sensorimotor cortex at both hemispheres according to a standardized protocol. To ensure low skin impedance (< 5 kΩ), the skin will be cleaned with a lotion and a non-allergic gel will be used for better transmitting of the signal (Ten20 conductive gel). Results will be expressed in % of suppression of mu activity. Patients may refuse QEEG measures at T1 and T2 due to the additional load of 20 minutes per assessment. If necessary due to allergy, nickel-free electrodes will be used.

### Compliance, integrity check and feasibility of mental practice

During the mental practice intervention period, therapy compliance of the patient is monitored by using a log in which the time spent on practice is recorded on a daily basis. The diary entries will be checked by either the therapist or a member of the nursing staff. In the Dutch guidelines the amount of therapy is considered of importance with regard to effectiveness of any intervention to improve functions [2,3,21].

Furthermore, a small sample of the participants will be interviewed by the researcher on experiences and beliefs during mental practice in the experimental group and on content of therapy as usual in the control group (n = 10 in each group for both sites). These will be selected arbitrarily, and limited to those agreeing.

The therapist will be monitored as well. They will be asked to what extent they followed the given instructions from the mental practice protocol. All therapists will be interviewed on their opinion of the feasibility of the experimental intervention in every day practice. To monitor the intervention content an external expert will attend therapy sessions of participants in the experimental group unannounced. Table 1 summarises the data collection.

**Table 1 T1:** Overview of used measures in this study

**Data**	**Time**	**Subject of assessment**
*Demographics*		
Age, gender, time post-stroke; weak side...	T0	Comparison at baseline
MMSE	T0	Comparison at baseline
Psychological assessment	T0	Comparison at baseline
Therapist' prediction on mental practice performance	T0	Comparison at baseline
*Prognostic variables*		
Amount of therapy/training	T0	Prediction on outcome
QEEG	T0	Prediction on outcome

*Primary outcome*		
11 point Likert scale: drinking and walking	T0, T1, T2	Performance on physical level 'activity'
11 point Likert scale: Patient specific tasks	T0, T1, T2	Performance on physical level 'activity'
*Secondary outcome*		
Motricity Index	T0, T1, T2	Performance on physical level 'function'
Barthel ADL scale	T0, T1, T2	Performance on physical level 'function'
Nine Hole Peg Test	T0, T1, T2	Performance on physical level 'function'
Berg Balance Scale	T0, T1, T2	Performance on physical level 'function'
Rivermead Mobility Index	T0, T1, T2	Performance on physical level 'activity'
Ten metres walk time	T0, T1, T2	Performance on physical level 'activity'
Timed up and go	T0, T1, T2	Performance on physical level 'activity'
Functional Ambulation Cat.	T0, T1, T2	Performance on physical level 'activity'
*Optional*		
QEEG	T1, T2	Performance on brain activity

*During six weeks intervention period*		
Log	Daily	
Interview	Once	A small sample (2× n = 10) will be interviewed to assess the patients opinion on feasibility of the program.
Co interventions	T1, T2	Process evaluation

*Measures with a mark are only used if required by the treating therapist (individual judgement)*.

### Randomisation, blinding and treatment allocation

#### Randomisation procedure

No stratification will take place [43]. Randomisation will take place on the participant level. Based on a computerized (block) randomisation schedule with random block size (4 or 6) seventy sequentially numbered envelopes will be prepared, with equality being achieved after every four or six. Each participant recruited will be registered and given the next sequential number, and then the envelope will be opened to determine their allocation. The randomisation procedure is the same for both sites.

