### Sample size calculation

The calculation of the sample size is based on the primary outcome measure, perceived improvement of daily activities, like 'drinking out of a cup' and 'walking', as assessed by an 11 point Likert scale. Although arbitrary, the calculation of the sample size is based on following expectations: For us a 20% difference between the two groups in this outcome measure would be a reasonable change to aim for which means a 2.2 point change on the Numeric Rating Scale (μ1 = 2.2). There is no literature available on the standard deviation in a stroke population but in other populations the standard deviation on numerical rating scales is somewhere between 1.5 and 3.0. In this sample size calculation we will use a standard deviation of 2.25 (σ = 2.25). The power (the ability to detect a true difference in outcome) of this study is set at 90% (β = 0.10). The level of significance (likelihood of detecting a treatment effect when no effect exists) is set at 5% (α = 0.05). The power and the level of significance are generally chosen by convention.

The sample size calculation formula used for measuring the difference between two unpaired samples is: N1 = N2 = (z_1-β _+ z_1-α/2_)^2 ^* ((σ_1_^2 ^+ σ_2 _^2^)/(μ_1 _- μ_2_)^2^)

This would mean that we would need to have 19 patients in each group assuming a 50:50 random allocation. The goal of this study is to have 35 patients in each group to allow for drop-outs, loss to follow-up and uncertainty in the power calculation. A sample size of n = 70 seems realistically achievable over a 2 year period. Two nursing homes participate in this study: Klevarie nursing home (Maastricht) assesses about 200 new stroke patients each year. nursing home St. Camillus (Roermond) treats another 70 patients each year. We estimate that 40% of all treated stroke patients will be able to participate in the study, but not all will want to. If an added value of the experimental intervention can not be found in 70 patients the clinical relevance of a mental practice-based therapy should be questioned.

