### Strategy vs tactics: teach how to do mental practice in general, or teach only a specific task?

Although all nursing homes work according to the best available evidence, there are considerable differences in tasks and organisation of the nursing homes, depending for instance if they are part of specific stroke services or not. This reflects in variations in time post stroke at submission, the neurological assessments, tasks of professionals and routeing of the patient during the rehabilitation process and also in the duration of the rehabilitation process. We wanted to create an intervention protocol that could be used in any nursing home, independent of the organisation form.

Second, we wanted therapists of different disciplines to use mental practice in motor learning tasks of the same patient, so that they could reinforce each other's therapy.

We therefore made the explicit choice to only set a fixed theoretical framework for using mental practice, but also leave room to tailor therapy to the preferences and abilities of the patient, thereby giving the professional space to use his/her experience (real practice) instead of forcing patients into a fixed intervention program.

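### One unstratified blocked sequence covers both nursing homes, so the blocks balance the trial total but neither home: a minor and cheaply avoided source of chance imbalance

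*Protocol article*

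**What the plan says.** The Sample size calculation section says "Two nursing homes participate in this study", one seeing about 200 new stroke patients a year and the other 70, with a target of 35 patients per arm.

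Under Randomisation procedure the protocol says "Randomisation will take place on the participant level" and "No stratification will take place", with a literature reference attached to the second statement. From a computer schedule with random block sizes of 4 or 6, "seventy sequentially numbered envelopes will be prepared", "with equality being achieved after every four or six". On enrolment: "Each participant recruited will be registered and given the next sequential number". The procedure is said to be identical at both sites, and no list per home is described.

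In the Discussion, the section on strategy versus tactics says "there are considerable differences in tasks and organisation of the nursing homes" and links this to when after stroke patients are admitted, how they are assessed, what staff do, the patient's route through care and how long rehabilitation lasts.

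The Multivariate analysis section adjusts for baseline variables only where this is judged necessary, and it does not name nursing home.

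**The concern.** A permuted block protects balance only within the list it belongs to. Here that list is the whole trial. Patients from the two homes enter the sequence in whatever order they are recruited, so each block may mix homes and the arms within a home are left to chance.

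Home is a natural factor to balance on. Usual care is the comparator and also the vehicle for the experimental treatment, and entry spans two to ten weeks after stroke. If case mix or care differs between the homes, a chance excess of one home in one arm shifts an unadjusted comparison. With 70 patients and only two homes, this is easy to prevent.

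**Working it through.** The protocol gives no figure for balance by home, so there is none of its own to reproduce.

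**Inputs**
- From the protocol: N = 70, 35 per arm, blocks of 4 or 6, target difference 2.2, SD 2.25, 20% dropout.
- Assumed: the smaller home's share of recruits follows its volume, 70/(200 + 70) = 0.26, or about 18 patients. Range examined: 0.15 to 0.50.
- Assumed: the homes differ by 1 point on the 0–10 scale, range 0.5 to 2. The protocol gives no figure for this.

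**1. Imbalance within the smaller home, shared list.** With 35 per arm and home independent of the sequence, the arm difference D in the smaller home has mean 0 and variance about 70 × p × (1 − p).
- p = 0.26: SD = √(70 × 0.259 × 0.741) = 3.67.
- Normal approximation with continuity correction: P(|D| ≥ 4) ≈ 2 × P(Z > 3.5/3.67) = 0.34; P(|D| ≥ 6) ≈ 2 × P(Z > 5.5/3.67) = 0.13.
- Simulation of the stated blocks (20,000 sequences) agrees: mean |D| 2.9, P(|D| ≥ 4) = 34%, P(|D| ≥ 6) = 14%, 95th percentile 7.
- Range of shares: P(|D| ≥ 4) = 24% at a share of 0.15 and 40% at 0.50.
- The overall arm difference never exceeded 2: the blocks do their job for the total, but not for the homes.

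**2. Effect on the estimate.** Shift = (D/35) × gap between homes.

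| Gap (assumed) | Shift at D = 6 | Share of 2.2 |
|---|---|---|
| 0.5 | 0.09 | 4% |
| 1 | 0.17 | 8% |
| 2 | 0.34 | 16% |

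At the mean imbalance of 2.9 and a 1-point gap the shift is 2.9/35 = 0.08.

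**3. Against sampling error.** SE = 2.25 × √(2/35) = 0.54. The 0.17 shift is 0.17/0.54, about a third of one standard error.

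**4. Precision.** Between-home variance adds p(1 − p) × gap² to the outcome variance if it is not already contained in the SD of 2.25. With 35 × 0.8 = 28 per arm after dropout, normal-approximation power is 95.5% without it.
- Gap 1: SD = √(5.06 + 0.19) = 2.29, power about 94.9%.
- Gap 2: SD = √(5.06 + 0.77) = 2.41, power about 92.6%.

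**5. With a separate blocked list per home** (10,000 simulated trials, share 0.26): mean |D| in the smaller home 0.7, 95th percentile 2, maximum 3, and no trial with 4 or more. The overall arm difference rises a little: mean 0.9 and maximum 6, against 0.5 and 2 with the shared list.

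**The case against.** The best defence is that unstratified permuted blocks over two sites are a legitimate scheme, chosen openly and with a reference (not available here). That stands. Four stronger readings might be inferred, and the documents support none of them.

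- *The treatment effect is confounded with home.* No. The expected imbalance is zero, and between-home variation belongs to the error variance of an unadjusted comparison, so type I error is not inflated. The 0.17 shift needs both a tail imbalance and an assumed gap.
- *The protocol says these two homes differ.* It speaks of nursing homes generally, to explain why the intervention should fit any of them. Applying this to the two trial homes is a fair inference, no more. That time since stroke differs between these two is stated nowhere.
- *One envelope sequence cannot serve two towns.* The text has patients registered and then numbered, which is compatible with central registration. If each home received its own contiguous run, the blocks would nearly balance each home and the figures above would not apply; but that is not described, and it would sit badly with ruling out stratification.
- *Leaving home out of the analysis is an error.* Covariate detail is commonly left to the analysis plan, which is not shown. The point rests on the allocation rule; the conditional adjustment means only that the article states no safeguard.

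One further objection stands as a cost. Patients and therapists know the allocation, so staff who see a complete local sequence in small blocks can guess the next assignment somewhat more easily than with a list shared between homes.

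**Conclusion.** The point holds as a minor design improvement. The stated rule balances the total and leaves balance within each home to chance: about a one-in-three probability of a difference of 4 or more among some 18 patients in the smaller home, and about 13% for 6 or more. This assumes a 26% share and recruits from the two homes mixing in one sequence. The consequence is modest: about 0.17 points at a 6-patient difference and a 1-point gap, well inside one standard error, and power stays above 90% even for a 2-point gap on the protocol's own SD. Validity and type I error are not in question. The change is still worthwhile, because the allocation rule cannot be repaired after enrolment, only adjusted for.

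**What to change.** 1. Generate a separate random-block list and numbered envelope set for each nursing home, keeping block sizes from site staff.
2. Include nursing home as a fixed, prespecified factor in the primary model whatever the observed imbalance, instead of adjusting only where judged necessary. This also lets the standard error reflect the stratified allocation.

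Cost: a second list and one degree of freedom; no added patients, visits or procedures. Local allocations become slightly more predictable to unblinded staff, which random, undisclosed block sizes limit. If that matters more than balance, keep the shared list and make change 2 alone; it removes the shift from an additive home difference without altering the envelopes.
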